| Sample size
Target sample size: 20                                                                                                                                                                                                                                                                                                                                                                                                                                                                                                                                                                                                                                                                                                                                                                                                                                                                                                                                                                                                                                                                                                                                                                                      | Approval date
2020-06-06, 1399/03/17                                                                                                                                                                                                                                                                                                                                                                                                                                                                                                                                                                                                        |
| Randomization (investigator's opinion)
Randomized                                                                                                                                                                                                                                                                                                                                                                                                                                                                                                                                                                                                                                                                                                                                                                                                                                                                                                                                                                                                                                                                                                                                                                       | Ethics committee reference number
IR.HUMS.REC.1399.165                                                                                                                                                                                                                                                                                                                                                                                                                                                                                                                                                                                      |
| Randomization description
Before assigning groups to individuals eligible to participate in the study, informed consent is completed for grouping individuals. the person who has no role in admitting patients and assigning patients to random codes preparing random sequences using online tools ( https://www.sealedenvelope.com/ ) and by permuted block randomization method. Individualized random allocation is done in blocks with sizes 2 and 4, and with stratification based on gender. eligibility criteria are monitored by the person responsible for admitting patients. Codes in a random sequence are assigned to patients by the treatment team without knowing that each code is in the intervention or placebo group. Patient codes are then matched to randomly generated                                                                                                                                                                                                                                                                                                                                                                          | Health conditions studied
1
Description of health condition studied
Laboratory confirmed COVID-19
ICD-10 code
U07.1
ICD-10 code description
COVID-19, virus identified                                                                                                                                                                                                                                                                                                                                                                                                                        |

## Primary outcomes

### 1

#### **Description**

Respiratory rate

#### **Timepoint**

At the beginning of the study (before the intervention) and day 5 after the intervention

#### **Method of measurement**

Pulse oximeter

### 2

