#### Participants

This study will be performed at Shahid Mohammadi Hospital in Bandar Abbas, Hormozgan in Iran. All positive (PCR confirmed) COVID-19 patients ≤65 years old who have Hb ≤9 and at least one of the severe COVID-19 symptoms (tachypnea (breathing rate > 30 beats per minute), hypoxemia (O2 ≤93 saturation, the partial pressure ratio of arterial oxygen <300), Lung infiltration (> 50% of lung field within 24 to 48 hours), progressive lymphopenia, LDH >245 U/l, CRP >100) and are willing to cooperate in this project will be included in the study. Patients with a history of coronary heart disease, thrombosis, deep vein thrombosis, chronic lung disease, diabetes mellitus, weakened immune system, end-stage renal disease, liver disease, and patients with a history of taking oral contraceptive pills, systolic blood pressure more than 160 mm Hg, diastolic blood pressure more than 90 mm Hg and age over 65 and erythropoietin above 500 are excluded.

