### **Intervention and comparator**

Patients will receive the standard of care (SOC) based on the treatment protocols of the Iranian National Committee of COVID-19 and recombinant erythropoietin (EPREX Manufactured by Johnson and Johnson Pharmaceutical Company) 300 units / Kg or 4000IU as subcutaneous (SQ) injection three times a day for 5 days and simultaneously Enoxaparin 1 mg/kg SQ daily is also taken to prevent thrombosis in the intervention group. Patients' blood pressure, along with other vital signs, are checked regularly and at regular intervals. In the control group, patients received SOC and the placebo (distilled water) is given as a subcutaneous injection three times a day for 5 days We use sterile water for injection (EXIR pharmaceutical company) as the placebo. To the same appearance of the placebo and the recombinant erythropoietin, they are taken in a separate room in the same size syringes and cover with labels before injection.

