### **Main outcomes**

The main outcome for this study is a composite endpoint for Patient clinical symptoms (Respiratory rate, Oxygen saturation state and arterial oxygen partial pressure ratio, Lung infiltration status, blood pressure), Laboratory tests (LDH, CRP, Lymphocyte count, Endogenous erythropoietin, and Haemoglobin level). All of these will be assessed at the beginning of the study (before the intervention) and day 5 after the intervention. The study will also evaluate side effects and how to manage them.

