### **Numbers to be randomised (sample size)**

A total of 20 patients will participate in this study, who are randomly allocated to the 2 arms with a 1:1 ratio; 10 patients in the intervention group will receive SOC and recombinant erythropoietin, and 10 patients in the control group will receive SOC and placebo.

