| Inclusion/Exclusion criteria
Inclusion criteria:
All definitively positive COVID-19 patients with Hb $\leq$ 9. Having at least one of the severe symptoms of COVID-19, including tachypnea (breathing rate> 30 beats per minute), hypoxemia (O 2 $\leq$ 93 saturation, the partial pressure ratio of arterial oxygen <300), Lung infiltration (> 50% of lung field within 24 to 48 hours), progressive lymphopenia, LDH>245 U/l, CRP>100
Exclusion criteria:
Patients with a history of coagulopathy Patients with a history of thrombosis Patients with a history of deep vein thrombosis Patients with a history of chronic lung disease Patients with a history of diabetes mellitus Patients with weakened immune systems Patients with a history of end stage renal disease Patients with liver disease Patients with a history of taking oral contraceptive pills (OCPs) Patients with systolic blood pressure greater than 160 mmHg Patients with diastolic blood pressure greater than 90 mmHg Patients over 65 years of age Patients with erythropoietin above 500 Patients with a history of myocardial infarction or unstable angina Patients with a history of malignancy | Assignment
Parallel                                                                                                                                                                                                                                                                                                                                                                                                                                                                                                                                                                                                                         |

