#### **Description**

Oxygen saturation state and arterial oxygen partial pressure ratio

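### Primary outcome 1, respiratory rate, has a pulse oximeter as its only stated method, which does not measure it; separately, the tachypnea limit carries the wrong unit

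*Protocol*

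**What the plan says.** The list of primary outcomes in the Protocol's registration record opens with "Respiratory rate", assessed before the intervention and on day 5. Its Method of measurement field reads "Pulse oximeter".

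The second primary outcome, "Oxygen saturation state and arterial oxygen partial pressure ratio", has an identical method entry of its own.

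Two other places mention respiratory rate or vital signs without saying how breathing is measured:

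- Main outcomes in the abstract lists it as a component of the composite: "Respiratory rate, Oxygen saturation state and arterial oxygen partial pressure ratio, Lung infiltration status, blood pressure".
- Intervention and comparator says "Patients' blood pressure, along with other vital signs, are checked regularly and at regular intervals".

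Breathing rate is also an entry sign. Participants in the abstract gives it as "tachypnea (breathing rate > 30 beats per minute", and the Inclusion/Exclusion criteria of the registration record repeat it as "tachypnea (breathing rate> 30 beats per minute". In both places it is one of several alternative signs of severe disease, of which a patient needs at least one.

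**The concern.** A primary outcome needs a method that can produce it. A pulse oximeter is the natural instrument for the saturation part of outcome 2. For respiratory rate it is not, unless the model also derives a breathing rate, and the Protocol does not say that it does. Staff who follow the entry literally have no respiratory rate to write down and must find their own way of getting one. That way may differ between staff, between the two time points or between arms.

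The last possibility matters here because the Protocol says that health care personnel, data collectors and outcome evaluators all know the allocation. An unspecified method in unblinded hands leaves room for differences between arms that have nothing to do with treatment.

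The unit error is a smaller matter. Beats per minute is a unit for pulse, not breathing, and it stands in both statements of the entry limit, so it should be corrected together with the method.

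**Working it through.** No arithmetic applies to the main point, because the Protocol gives no figure that depends on how respiratory rate is measured. The check is a reading of the relevant entries side by side.

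**1. Could the entry be displaced by the reading of the PDF?** The eight primary outcomes and their methods pair as follows:

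| Outcome | Stated method |
|---|---|
| 1. Respiratory rate | Pulse oximeter |
| 2. Oxygen saturation and partial pressure ratio | Pulse oximeter |
| 3. Lung infiltration | Chest x-ray |
| 4 to 7. LDH, CRP, lymphocytes, endogenous erythropoietin | Laboratory |
| 8. Blood pressure | Sphygmomanometer |

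The entry for outcome 1 stands before the number that opens outcome 2. Outcome 2 has its own oximeter entry, and outcomes 3 to 8 match their instruments. A shift by one line would have broken those later pairs, so the entry belongs to respiratory rate.

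**2. Is another method given elsewhere?** Main outcomes names the variable only. The vital-signs sentence in Intervention and comparator names no method. The same sentence appears in the registration record's description of the intervention group but not in that of the control group. The oximeter entry is therefore the sole instruction.

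**3. Can the stated instrument yield the outcome?** This depends on the device, which the Protocol does not describe.

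- If it shows saturation and pulse only, as an ordinary oximeter does, it yields no respiratory rate.
- If it also derives a respiratory rate, the outcome could be obtained, but the Protocol would be relying on a feature that it does not mention.

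In both cases the entry needs correcting.

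**4. What quantity is intended?** The outcome is called respiratory rate in Main outcomes and in the outcome list. The entry sign is called tachypnea and breathing rate in both places. Every mention is of breathing, so beats per minute is a wrong label on a quantity that is otherwise clearly named.

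**5. How much work is the correction?** The sample-size section says "A total of 20 patients will participate in this study", and the outcome has two time points: 20 × 2 = 40 counts of about one minute each, or about 40 minutes over the whole trial.

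**The case against.** The strongest reply is that this is a mismatch in a registry field together with a unit slip. Staff know what a respiratory rate is, and every section names breathing. The Protocol does not describe the oximeter, so it cannot be excluded that the model derives a rate. Respiratory rate is one of eight listed primary outcomes, and being listed first is only the order of the record. Most of this stands, and it limits the severity. It does not remove the point, because the method entry is the only instruction for a primary outcome and it does not fit that outcome.

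Three stronger readings are tempting and are not supported:

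- **That the trial records pulse in place of breathing.** A reader might infer this from the oximeter and beats per minute taken together. No section says that pulse is recorded, and the unit slip is in the eligibility text, not in the definition of the outcome.
- **That every patient would meet the tachypnea sign, since any pulse exceeds 30.** This requires staff to enter a pulse as a breathing rate, which nothing in the Protocol suggests. Tachypnea is also only one of several alternative signs, so a change in enrolment is not shown.
- **That a stated amount of power is lost.** The Protocol gives no effect size, standard deviation or power, and no correlation between pulse and breathing. Any such figure would rest entirely on outside assumptions, so none is offered here.

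There is also a fair objection to the remedy. A manual count by someone who knows the allocation can be biased. That is true and is counted as a cost below.

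**Conclusion.** The point holds in a limited form. The method stated for primary outcome 1 does not measure respiratory rate with an ordinary pulse oximeter, and no other section of the Protocol repairs this. The unit of the tachypnea limit is wrong in two places, although its meaning is clear.

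Severity is moderate. One of eight listed primary outcomes is affected. The sample size is not touched, and there is no evidence that any recorded value is wrong. The conclusion rests on one assumption about the device, namely that it shows saturation and pulse only. If it does derive a respiratory rate, the fault becomes an undocumented method, and the entry still needs correcting.

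**What to change.** - In Primary outcomes, item 1, Method of measurement, replace the oximeter with a breath count by direct observation over a full 60 seconds, patient at rest, done the same way in both arms at baseline and on day 5.
- In Participants (abstract) and in the Inclusion/Exclusion criteria of the registration record, change beats per minute to breaths per minute. The limit itself is not in question here.
- For patients already enrolled, record for each value how the respiratory rate was obtained. Use a charted count where one exists; the Protocol does not describe such records, so they cannot be presumed, least of all in the control group. Do not enter a displayed pulse rate as a respiratory rate. A value that the device actually derived as a respiratory rate need not be discarded on principle, but its source should be stated.

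The cost is a wording change in two parts of the Protocol and about one minute per assessment, with no new equipment. There are two drawbacks. A manual count by assessors who know the allocation is open to some observer bias; a fixed duration and the same procedure in both arms limit this but do not remove it. Values from patients enrolled before and after the change may come from different methods, which is why the source of each should be on record before the analysis. The Protocol's Trial Status section says that recruitment was still open, so the correction can still govern values not yet collected.

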#### **Description**

Oxygen saturation state and arterial oxygen partial pressure ratio

#### **Timepoint**

At the beginning of the study (before the intervention) and day 5 after the intervention

#### **Method of measurement**

Pulse oximeter

### 3

#### **Description**

Lung infiltration status

#### **Timepoint**

At the beginning of the study (before the intervention) and day 5 after the intervention

#### **Method of measurement**

chest x-ray

### 4

#### **Description**

LDH level's

#### **Timepoint**

At the beginning of the study (before the intervention) and day 5 after the intervention

#### **Method of measurement**

pathobiology laboratory

### 5

#### **Description**

CRP level's

#### **Timepoint**

At the beginning of the study (before the intervention) and day 5 after the intervention

#### **Method of measurement**

pathobiology laboratory

### 6

#### **Description**

Lymphocyte count

#### **Timepoint**

At the beginning of the study (before the intervention) and day 5 after the intervention

#### **Method of measurement**

pathobiology laboratory

### 7

#### **Description**

Endogenous erythropoietin level's

#### **Timepoint**

Beginning of study (before intervention)

#### **Method of measurement**

Pathobiology laboratory

### 8

#### **Description**

Patients' blood pressure

#### **Timepoint**

At the beginning of the study (before the intervention), during the intervention (5-day erythropoietin administration)

#### **Method of measurement**

Sphygmomanometer

## Secondary outcomes

### 1

#### **Description**

Patients' blood hemoglobin levels

#### **Timepoint**

Start of study (before the intervention), day 5 after the intervention and 2 to 4 weeks after the intervention

#### **Method of measurement**

Pathobiology laboratory

## Intervention groups

### 1

#### **Category**

2**Description**

Control group: Group B: The standard drug treatment is based on the treatment protocols of the National Committee for COVID-19 and the placebo (distilled water) is given as a subcutaneous injection five times a day for 5 days. Standard drug treatment according to the treatment protocols of the National Committee for COVID-19 includes Hydroxychloroquine / Chloroquine Phosphate: • Hydroxychloroquine sulfate tablets 200 mg or chloroquine phosphate tablets 250 mg (equivalent to 150 mg base dose) 2 tablets every 12 hours on the first day and then one tablet every 12 hours for at least 7 days and up to 14 days. One of the following medications at the discretion and diagnosis of the treating physician: • Caltrate tablets (Lopinavir / Ritonavir) 50/200 mg every 12 hours 2 pieces after meals for at least 7 days and a maximum of 14 days • Tablets (Atazanavir / Ritonavir) 300/100 One tablet daily with food or Atazanavir 400 mg daily for at least 7 days and up to 14 days

**Category**

Placebo

**Title of funding source**

Bandare-abbas University of Medical Sciences

**Proportion provided by this source**

100

**Public or private sector**

Public

**Domestic or foreign origin**

Domestic

**Category of foreign source of funding**

empty

**Country of origin****Type of organization providing the funding**

Academic

**Sharing plan****Deidentified Individual Participant Data Set (IPD)**

Undecided - It is not yet known if there will be a plan to make this available

**Study Protocol**

Undecided - It is not yet known if there will be a plan to make this available

**Statistical Analysis Plan**

Undecided - It is not yet known if there will be a plan to make this available

**Informed Consent Form**

Undecided - It is not yet known if there will be a plan to make this available

**Clinical Study Report**

Undecided - It is not yet known if there will be a plan to make this available

**Analytic Code**

Undecided - It is not yet known if there will be a plan to make this available

**Data Dictionary**

Undecided - It is not yet known if there will be a plan to make this available
